#### Recruitment

We will utilize a multifaceted recruitment effort including both active and passive approaches. Outreach will be primarily conducted through advertisements on popular social media and dating apps. Potential participants will be able to complete the eligibility screener directly from these advertisements and, if eligible, will be contacted by study staff to begin the process of enrollment into the study. Other avenues of recruitment, such as organized outreach through community-based organizations as well as bars and community events will also be utilized.

Prescreened eligible participants obtained through the online screener will be automatically emailed a screening link to be sent to their main partner. If eligible, participants will be contacted by study staff via phone calls, texts, and emails to schedule a remote visit to determine final eligibility and participants will review and complete the consent document. Both will then have their baseline appointment scheduled and have their home-based surveys emailed to them. Once their home-based surveys are completed, Molecular Testing Labs (MTL) STI/drug and HIV testing kits will be mailed to the participants’ home(s).

### Methods: assignment of interventions

#### Randomization

Couples will be randomly assigned to 1 of 4 conditions, CHTC as usual, CHTC + SUM, CHTC + CT video, or CHTC + SUM + CT video using a stratified block randomization procedure programmed in Qualtrics. Specifically, randomization will account for baseline report of: (1) relationship length (4 years or less/greater than 4 years) and (2) race/ethnicity makeup of the couple, for example, both partners identify as white and non-Hispanic/one or both partners identify as non-white or Hispanic. The random assignment will be performed by the assigned study interventionist immediately prior to intervention delivery.

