### Interventions

All participants, regardless of condition, will complete a CHTC session. Completion of CHTC involves 8-steps: 1.) Introduce CHTC and Obtain Concurrence: an introduction to the CHTC process and receiving the couples consent; 2.) Prepare For and Conduct HIV Test: explanation of the HIV test itself and possible results couples could receive, followed by a rapid HIV test; 3.) Explore Couple’s Relationship: an exploration of the couple’s relationship to build rapport; 4.) Discuss HIV Risk Concerns and Reasons for Seeking CHTC: discussion of current risks, reasons for testing and HIV prevention strategies (i.e. condom use, PrEP use, etc.); 5.) Discuss Couple’s Agreement: exploration of the couple’s sexual agreement and rules in regards to outside sexual partners; 6.) Provide Results: results are given to each member of the couple at the same time and can be the same (concordant negative or positive) or discordant; 7.) Develop Care, Treatment, and Prevention Plan Based on Result: discussion of future steps regarding HIV transmission risk prevention strategies (i.e. discussion of introducing condoms or PrEP use); and 8.) Link with Follow-up Services: referrals given in light of current HIV test results (i.e. referrals for confirmatory testing and other health services).

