### Communication training (CT) videos

The CT video component is designed to be self-delivered. Four couples are depicted in separate scenes discussing HIV testing, drug use, sexual agreements, and drug use during sex. Each scene is viewed twice. In the initial viewing, the couple in the video makes one or more communication errors. The scene is subsequently viewed a second time and the couple utilizes more effective communication skills, resulting in a more adaptive resolution. Each scene is introduced by a narrator who points out communication errors and orients viewers to skills utilized in adaptive versions of each scene.

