### Substance use module (SUM)

The SUM is administered after step 5 of CHTC and prior to the delivery of rapid HIV-test results. The couple is first asked to fill in a calendar for the past 30 days, indicating each day on which either member used drugs or consumed alcohol. Completion of the calendar is done using an excel spreadsheet displayed on a shared computer screen to facilitate remote intervention delivery. After completion of the calendar, the HIV tester asks a series of debriefing questions designed to elicit the couples’ perspective on their use, establish the couple’s goals and limits for drug use, and make plans to achieve these goals.

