### Fidelity monitoring and supervision

Drs. [name] or [name] provide feedback on all mocks based upon review of audio recordings. In addition, mock sessions are recorded and fidelity assessed using the CDC’s CHTC fidelity checklist [33]. Fidelity to MI during SUM completion is evaluated using a modified version of the Motivational Interviewing Treatment Integrity system Moyers et al. [11] augmented with codes developed by [name] et al. [21] specifically to assess the fidelity of MI delivered to couples.

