#### Blinding

Study staff delivering intervention cannot be blinded to the condition they are delivering. Assessment staff are blinded to the condition at baseline and follow-up. There are no anticipated circumstances that would result in unblinding of assessors during the trial. Participants cannot be blinded to their assigned arm. The arms are described in the informed consent process and it is reasonable that participants will be able to deduce whether or not they viewed the CT videos and discussed drug use during their session.

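### The interventionist draws the full four-arm assignment before the session and so knows the SUM arm during shared CHTC steps 1–5, where delivery could differ by arm; this knowledge is avoidable

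*Protocol article*

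**What the plan says.** Four sections of the protocol article bear on this point.

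- **Randomization.** Couples are allocated to one of four conditions "using a stratified block randomization procedure programmed in Qualtrics". On who draws and when, the text is: "The random assignment will be performed by the assigned study interventionist immediately prior to intervention delivery".
- **Interventions.** CHTC is the common background: "All participants, regardless of condition, will complete a CHTC session". It has eight steps. Step 4 is described as "discussion of current risks, reasons for testing and HIV prevention strategies", and step 5 explores the couple's sexual agreement.
- **Substance use module (SUM).** The place of the module in the session is fixed: "The SUM is administered after step 5 of CHTC and prior to the delivery of rapid HIV-test results".
- **Blinding.** On providers, the statement covers the condition as a whole: "Study staff delivering intervention cannot be blinded to the condition they are delivering". Outcome assessors are blinded.

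**The concern.** The trial asks what the SUM and the communication training (CT) video add to CHTC. The SUM contrast answers that only if the rest of CHTC is delivered in the same way with and without the module. Until the end of step 5, SUM and non-SUM sessions have no reason to differ, yet the person leading them already knows which kind of session it is.

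That knowledge could act in several ways. A provider who knows that no SUM will follow might bring drug use into the risk discussion to make up for it, which would dilute the SUM contrast. A provider who knows that a SUM will follow might prime the topic early, which would inflate the contrast. Or the provider might defer the topic and shorten the agreement discussion, which bears on the transmission risk outcomes.

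At stake is the interpretation of the primary hypothesis that the SUM reduces drug use and drug-related problems. Any difference in steps 1–5 that follows the SUM arm would be counted in the estimated SUM effect, and no analysis of the outcome data could separate the two.

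**Working it through.** No figure in the article depends on this point, so there is nothing to recompute. The check sets the sections side by side.

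1. **When the provider learns the arm.** Randomization puts the draw in the interventionist's hands just before intervention delivery. I read intervention delivery as the start of the CHTC session. That is the natural reading, although the article does not spell it out. The draw yields one of four conditions, so it discloses the SUM and CT elements together.

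2. **When SUM and non-SUM sessions first need to differ.** The SUM section places the module after step 5 and before results, which are step 6.

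3. **The interval between the two.** Steps 1–5 are introduction and concurrence, the HIV test, the relationship, risk concerns, and the agreement. These are 5 of 8 steps, delivered with knowledge of the SUM arm in every session. This counts exposure to a possible bias; it does not measure bias.

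4. **Whether the provider has room to act on the knowledge.** Steps 4 and 5 are open discussions. Under Eligibility criteria, every couple includes a man who reports illicit drug use in the past 30 days, so the subject can readily arise. Under Intervention training, all interventionists are trained in motivational interviewing with couples, and the last three of the four CHTC mocks include the SUM. The article describes no separate group of providers for the non-SUM arms.

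5. **Whether anything described would detect a difference.** Fidelity monitoring and supervision says: "In addition, mock sessions are recorded and fidelity assessed using the CDC’s CHTC fidelity checklist". The other check covers motivational interviewing during the SUM itself. Neither compares steps 1–5 between arms in trial sessions. Blinded assessors protect outcome measurement, not treatment delivery.

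6. **Whether the knowledge is needed.** For the SUM element it is not needed before the end of step 5. The same interventionist then continues with either the module or the results, and the draw already runs in software. For the CT element the answer is open: "The CT video component is designed to be self-delivered", but the article does not say when the video is viewed relative to the CHTC steps.

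7. **Whether session length would reveal the arm.** The draw comes immediately before delivery, so the appointment has to be booked before the arm is known. Slot length therefore cannot reveal the SUM assignment, and masking requires no change to booking.

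**The case against.** The strongest reply is that nothing here is false or contradictory. Staff who lead the SUM cannot be blinded to it, and the Blinding section makes no claim about steps 1–5. A programmed, stratified draw made late and after baseline is sound practice for concealment. CHTC is a structured procedure taught from one curriculum at both sites, and drug use is also measured by urine assay. The article condenses a fuller protocol, which may contain fidelity review of trial sessions. Masking would also protect only part of the session: a provider inclined to compensate could still do so in step 7, the care and prevention plan.

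Much of this stands. The point is an avoidable weakness in the design, not an error of fact. Structure and training reduce the room for drift but do not remove it from open discussions. A urine assay does not help if drug use itself changes because steps 1–5 were delivered differently. The limit at steps 6–8 is real, but it is no reason to leave steps 1–5 exposed.

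Three stronger readings are tempting, and the documents do not support them.

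- A reader might infer that the common CHTC treatment does differ by arm. No section says or shows this, and the plausible behaviours pull in opposite directions.
- A reader might infer that the early draw serves no purpose. One draw assigns both factors, and the CT video may be due before or at the start of the session. This could justify an early draw, but not early disclosure of the SUM element.
- A reader might infer that couples who leave between the draw and step 5 dilute the effect by a known amount. The article gives no rate for such losses.

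**Conclusion.** The point holds as a possible performance bias in the SUM contrast. It is avoidable for steps 1–5, and no check described in the article would detect it. The provider's knowledge of the SUM arm follows directly from the text. Differential delivery is a risk only, of unknown direction and unknown size.

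The conclusion rests on two assumptions: that intervention delivery begins with CHTC step 1, and that the interventionist who draws the assignment sees all of it. If the full protocol already masks the SUM element, the point falls. If it provides for fidelity ratings of trial sessions compared by arm, the remaining risk is smaller. The change is worth making because it is cheap and protects the primary contrast, but the concern does not invalidate the design.

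**What to change.** Keep one stratified four-arm draw in Qualtrics before the session, with the strata and allocation unchanged. Show the CT element when it is needed, and state in the protocol when the video is viewed. Have Qualtrics withhold the SUM element from both interventionist and couple until the interventionist logs completion of step 5. It then displays either the SUM or an instruction to go on to step 6.

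Amend Randomization to describe this staged display. Amend Blinding to say that interventionists are unaware of the SUM assignment during steps 1–5 and aware of it from then on.

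State that every randomised couple, including any that leaves before step 5, stays in the intent-to-treat analysis under its drawn arm. The assignment exists from the moment of the draw; only its display is delayed. Treating early leavers as not randomised to the SUM would break the four-arm factorial and conflict with the commitment in the Data analysis plan to analyse all randomised couples.

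The cost is modest programming, a few amended sentences and a small extra operational step in mid-session. Steps 6–8 stay unblinded, and the CT element is not masked. If staged display proves impractical, a weaker alternative is to record trial sessions and have raters who do not know the arm score CHTC fidelity for steps 1–5, reported by arm. That would detect a difference but not prevent one.

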#### Blinding

Study staff delivering intervention cannot be blinded to the condition they are delivering. Assessment staff are blinded to the condition at baseline and follow-up. There are no anticipated circumstances that would result in unblinding of assessors during the trial. Participants cannot be blinded to their assigned arm. The arms are described in the informed consent process and it is reasonable that participants will be able to deduce whether or not they viewed the CT videos and discussed drug use during their session.

### Methods: data collection, management, and analyses

#### Data collection for primary outcomes

Self-report data for all primary outcomes will be gathered using a Research Assistant administered timeline follow-back (TLFB) interview [18] covering the past 30 days. The interview administration is facilitated by the use of a calendar data entry platform supported in Microsoft Access. The Research Assistant first identifies and records “anchor dates” or significant events on the calendar. Next, for participants who are prescribed PrEP, the Research Assistant records all days the participant indicated a missed dose of PrEP. Next, the Research Assistant records days on which the participant reported heavy drinking or the use of marijuana or other illicit drugs (i.e., cocaine or crack, MDMA, methamphetamine, ketamine, or GHB). Finally, the Research Assistant records sexual events. These entries included partner type (main or casual), the sex act performed (e.g., anal insertive, anal receptive), and whether a condom was used.

Biological testing is coordinated through Molecular Testing Laboratory (MTL). All specimens are self-collected at home using materials supplied directly by MTL. MTL also provides materials necessary for return shipping. Participants complete specimen collection during their remote baseline appointment so a Research Assistant is available to clarify specimen collection procedures, answer questions as they arise, and observe the preparation of specimens for shipment.

Urine drug testing will be completed using the urethral drug testing kit by Molecular Testing Labs. Participants are provided with a collection cup and are instructed on the process of correctly collecting a urine sample by trained study staff. The participant will use a provided pipette to transfer the urine into a collection tube that will be sent back to the lab for testing. This sample will be tested for the recent use of illicit drugs and results are available within 5-7 business days.

Tests for urethral STIs will be conducted on self-collected urine specimens, which will be packaged according to appropriate biosafety protocols for return mailing to the laboratory. Tests for rectal STIs will be conducted on a self-administered rectal swab, using a Q-Tip-like swab and with written and cartoon instructions that have been used to support over 5000 rectal swab collections by [name]’s team. The presence of *C. trachomatis* (CT) and N. gonorrhea (NG) in self-collected urethral and rectal specimens will determined by using the Abbott Real Time CT/NG assay, an FDA-cleared real-time polymerase chain reaction (PCR) assay for direct, qualitative detection of a region of the cryptic plasmid DNA of CT and the Opa gene of NG, as previously reported [5].

Syphilis testing will be conducted on Dried Blood Spots (DBS). MTL provides a lancet for finger stick blood draw and DBS card for specimen collection. Syphilis specimens are tested with an RPR test. Initially reactive results are reported as a positive screening test, with referral for providers. If enough plasma is not available for a “neat” initial RPR, a 1:4 dilution RPR will be conducted. If negative, the negative report will be reported with a note that it was on a 1:4 dilution. This procedure lowers the sensitivity of the RPR but would still be expected to perform well for primary and secondary syphilis infections, with the exception of very early infection.

HIV testing will be conducted with all participants who self-report an HIV-negative or unknown HIV status at baseline in the context of CHTC regardless of intervention condition. Testing will be performed using the Oraquick 4th generation testing kit. During the intervention session, the participants are guided through the process of completing the test by the interventionist. Participants will self-administer the test by rubbing the testing strip against the gum-line and allowing the test to rest in the provided developing liquid for a rapid result. Results are available in 20 min and delivered to participants immediately. At follow-up, HIV-testing will be conducted individually, allowing participants the option of an Oraquick HIV test or a self-administered dried blood-spot (DBS) test to complete their HIV test.

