The use of illicit drugs has been consistently linked to sexual risk taking among SMM. In particular, the use of a number of illicit drugs (i.e., cocaine or crack, methamphetamine, ecstasy, ketamine, gamma-hydroxybuterate – GHB) has been associated with either the occurrence or frequency of CAS with casual partners across a range of studies (e.g., [1, 15, 16, 22, 23]). In their recent paper, [name] et al. examined data from a sample of more than 65,000 SMM and found that this association was significant across relationship status and sexual agreements, though it was significantly stronger among single and non-monogamous men compared to those in monogamous relationships [22]. Separately, [name] et al. [28] have since observed an association between illicit drug use and CAS with casual partners in day-level data obtained from male couples.

[name] et al. [20] posited that CHTC – which in its standard form involves the negotiation of a sexual agreement and joint HIV prevention planning – might provide an opportunity for male couples to develop consensus related to rules or limitations on drug use. Furthermore, they hypothesized that augmenting CHTC with supplemental communication skills training might also enhance its efficacy. The team developed a communication training (CT) video to deliver dyadic skills training following a standard Cognitive Behavioral modeling paradigm. They also developed a substance use module (SUM) wherein partners create a calendar feedback tool, which is subsequently debriefed using a brief dose of Motivational Interviewing (MI). The MI component is delivered following the framework for couples MI derived by [name] et al. [24, 27].

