### Eligibility criteria

Participants must fulfill the following inclusion criteria to be enrolled in the study. In each couple, both partners must indicate cismale gender and be 17 years of age or older. In addition, at least one participant in each couple must (1) be aged 17 to 29 years; (2) self-report an HIV-negative or unknown sero-status; (3) report use of at least 1 illicit drug (cocaine/crack, opiates, misuse of prescription medication, stimulants, psychedelics, ecstasy, ketamine, GHB) in the past 30 days, (4) have engaged in CAS with a casual partner or a main partner who is non-monogamous or sero-discordant in the past 90 days, (5) live in the New York City or Detroit metropolitan area, and (6) be able to speak and read in English.

Participants will be excluded from the study if they indicate signs of acute suicidality; gross impairment in cognitive functioning; or any history of intimate partner violence and current safety concerns in the current relationship. The trial does not place restrictions on concomitant receipt of care for substance use or HIV prevention.

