### Primary outcomes

#### Illicit drug use

Will be operationalized as the odds of drug use in the past 30 days indicated by self-report on the Time-line Follow-back (TLFB) interview. Biologically, the occurrence of drug use will be assessed via urine assay.

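### The timeline follow-back drug list omits classes that qualify a couple for entry, so some eligible users would score as non-users on the primary drug-use outcome; whether marijuana counts is not stated

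*Protocol article*

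**What the plan says.** Three sections of the protocol article bear on this.

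- **Eligibility criteria.** At least one partner must "report use of at least 1 illicit drug (cocaine/crack, opiates, misuse of prescription medication, stimulants, psychedelics, ecstasy, ketamine, GHB) in the past 30 days". Marijuana is not on this list.
- **Primary outcomes, Illicit drug use.** The outcome "Will be operationalized as the odds of drug use in the past 30 days indicated by self-report on the Time-line Follow-back (TLFB) interview". No drug classes are named. A second measure follows: "Biologically, the occurrence of drug use will be assessed via urine assay".
- **Data collection for primary outcomes.** "Self-report data for all primary outcomes will be gathered using a Research Assistant administered timeline follow-back (TLFB) interview", covering 30 days. The interviewer records days of heavy drinking or "the use of marijuana or other illicit drugs (i.e., cocaine or crack, MDMA, methamphetamine, ketamine, or GHB"). On the urine specimen the section says only "This sample will be tested for the recent use of illicit drugs", without naming the panel.

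The Background names the drugs that earlier studies linked to sexual risk as "cocaine or crack, methamphetamine, ecstasy, ketamine, gamma-hydroxybuterate". These are the five TLFB drugs without marijuana.

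**The concern.** Entry and outcome both use a 30-day window, but the drugs they cover are not the same. If the interview has no place for a class that brought a participant into the trial, his use of it is never written down. He starts the trial as a non-user on the primary self-report outcome and has no recordable use to give up.

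The primary model (Primary analyses of intervention effects) takes its first slope from baseline to post-intervention, so such a participant adds no visible change whatever the modules do for him. The same variable is the proposed route to lower HIV transmission risk behavior (Objectives), so an incomplete measure also weakens the mediation analysis.

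A scoring rule can be settled later in an analysis plan. Days of use that the interview never recorded cannot be recovered.

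**Working it through.** **Step 1: set the two lists side by side.**

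| Class | Qualifies for entry | Recorded on TLFB |
|---|---|---|
| Cocaine/crack | yes | yes |
| Ecstasy/MDMA | yes | yes |
| Ketamine | yes | yes |
| GHB | yes | yes |
| Methamphetamine | yes, as a stimulant | yes |
| Other stimulants | yes | no |
| Opiates | yes | no |
| Misused prescription medication | yes | no |
| Psychedelics | yes | no |
| Marijuana | no | yes |

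The point rests on this comparison and needs no figure.

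**Step 2: the plan's own power figure.** Sample size states power above .80 for a 15% reduction in the odds of drug use with 240 couples (480 individuals). The reference rate, within-couple correlation and alpha of the simulation are not given, so this can be neither reproduced nor refuted. It is background only.

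**Step 3: direction and possible size of the dilution (illustration).** Inputs from the article: 480 individuals, hence 480/2 = 240 per level of one factor. Everything else is assumed: two-sided alpha .05, within-couple correlation 0.3, 50% versus 35% using any qualifying drug, and one share f of users, equal in both arms, who use only unlisted classes.

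- Effective n per level = 240/(1 + 0.3) = 184.6.
- Observed rates are p1(1 − f) and p2(1 − f), so the observed difference is 0.15 × (1 − f).
- Power = Φ{[d − 1.96·√(2p̄(1 − p̄)/n)] / √[(p1(1 − p1) + p2(1 − p2))/n]}, where d is the observed difference and p1, p2 are the observed rates.
- For f = 0: (0.15 − 1.96 × 0.0515)/0.0509 = 0.97, so power is .83.

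| f | Observed rates | Difference | Odds ratio | Power |
|---|---|---|---|---|
| 0 | .50 vs .35 | 15.0 points | 0.54 | .83 |
| 10% | .45 vs .315 | 13.5 points | 0.56 | .76 |
| 20% | .40 vs .28 | 12.0 points | 0.58 | .68 |
| 30% | .35 vs .245 | 10.5 points | 0.60 | .60 |

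The odds ratio is p2/(1 − p2) divided by p1/(1 − p1); at f = 20%, (.28/.72)/(.40/.60) = 0.58. Under this set-up the risk ratio stays at 0.70. What is lost is absolute difference and precision, and the odds ratio moves modestly towards 1.

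**Step 4: marijuana, only if it is scored.** Suppose a share m uses marijuana, independently of other drugs and unchanged by the intervention. The observed rate is 1 − (1 − p)(1 − m), so the difference is 0.15 × (1 − m). For m = 20, 40 and 60% it is 12, 9 and 6 points, with power .64, .44 and .28.

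**Limits.** This is a two-proportion test at one time point, not the five-point growth model. The 15-point effect is a choice: the article's 15% is stated on the odds, and a literal odds ratio of 0.85 gives this approximation power of only about .09 to .14 over control rates of .3 to .8 and correlations of 0 to 0.5. Neither f nor m is in the article.

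**The case against.** **The list may be illustrative.** The Interventions section uses *i.e.* together with *etc.*, so the author's *i.e.* can be loose, and a parenthesis in a condensed article may not be the whole Access form. This lowers certainty. Against it, the data-collection section uses *e.g.* correctly a few lines later, and the Background gives the same five drugs after *i.e.* If the list is only illustrative, the text still needs correcting.

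**A narrower endpoint may be intended.** The five drugs are those tied to condomless sex in the Background, and club drugs are a keyword. Wide entry with an endpoint on risk-linked drugs is defensible, but the article does not say this is the intention.

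**Other measures exist.** Urine testing could catch some missed use, and DAST scores, which Sample size powers separately, do not depend on the TLFB list. Both help. However, the self-report outcome is defined on the TLFB, the urine panel is not given, and a test for recent use is not shown to cover 30 days.

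**The harm is limited to exclusive users.** Someone who uses both a listed and an unlisted class is still captured as a user. Because the drug criterion sits among those that "at least one participant in each couple must (1) be aged 17 to 29 years" introduces, only one partner need be a user, so some baseline non-users are expected by design. This stands, and it bounds the problem to users of unlisted classes alone.

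**Marijuana.** A reader might infer that marijuana use is scored as drug use in the primary outcome. The documents do not support that. The data-collection section says what is recorded, heavy drinking included. The outcome is headed as illicit drug use, and the entry list of illicit drugs omits marijuana. The wording in the data-collection section points the other way, so the matter is open. Nor is bias towards the null certain if marijuana is scored: the SUM sets goals for drug use generally and might reduce marijuana use too.

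**Conclusion.** The mismatch is real as printed. Opiates, misused prescription medication, psychedelics and stimulants other than cocaine/crack, MDMA and methamphetamine can bring a couple into the trial but are not among the drugs the TLFB is said to record. Users of those classes alone would score as non-users and could show no reduction, which dilutes the SUM and CT effects. This rests on reading the list as complete, so confidence is moderate.

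The marijuana problem is conditional on marijuana being counted, which the article leaves unstated.

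A reader might also take the power figures as the trial's actual loss. They are not: prevalence, correlation, effect size and both shares are assumed, and the article supplies none of them. What the text supports for the omitted classes is the direction of the dilution, not its size. The point should be settled early because the missing data cannot be rebuilt, but it does not show that the trial cannot meet its aim.

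**What to change.** 1. Extend the TLFB drug fields to cover every class in the eligibility list: add opiates, misused prescription medication, psychedelics and other stimulants. If the form already holds them, correct the description in the data-collection section.
2. Define the primary self-report outcome as any past-30-day use of those qualifying classes, and name them. If a narrower endpoint is intended, say so and give the reason.
3. Keep marijuana recorded, as heavy drinking is, but analyse it separately; or state explicitly that it counts towards the outcome and why.

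The cost is a few extra fields in the Access form, one sentence of outcome definition and slightly longer interviews. Any interviews already done on the shorter list should be flagged, because their unlisted use is unknown rather than absent.
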